**Figure 2 – Protocol Schematic (Group B)**

[figure not shown]

**Group C (Female patients with Reproductive Disorders):** Patients will attend for two study visits each, receiving kisspeptin-54 and 0.9% saline (placebo) (on separate visits and in

random order) via the intranasal route. The dose of kisspeptin-54 will be determined based on the results of *Group A* (described above) and will be the same dose examined in *Group B*. After self-administration of kisspeptin-54 or placebo at timepoint 0 minutes, serum levels of LH, FSH, oestradiol, and progesterone will be measured every 15 minutes for 4 hours (**see Figure 3**).

**Figure 3 – Protocol Schematic (Group C)**

[figure not shown]

For all groups: On arrival to the Clinical Research Unit and following a period of acclimatisation, an intravenous cannula will be inserted into one antecubital fossa (for blood sampling). Female participants will have their urine tested for  $\beta$ -hCG (pregnancy test) at each study visit to ensure that they are not pregnant. Next, participants will receive a standardised education session explaining the procedure of intranasal administration (to ensure good technique). Blood will then be sampled at timepoints -30, -15, and 0 minutes (pre-administration baseline), followed by intranasal administration of kisspeptin-54 or 0.9% saline (placebo).

Thereafter, serum levels of LH, FSH, and testosterone (*Group A*), or oestradiol and progesterone (*Group B* and *Group C*) will be measured every 15 minutes for 4 hours. Heart rate, blood pressure, and the presence of adverse symptoms will also be recorded every 15 minutes. At least two clinically trained investigators will be present throughout each study visit.

Participants, study visit investigators, and the data analysts will be blinded to the identity of kisspeptin or placebo. The order of study visits will be randomised by an independent investigator prior to recruitment of the first participant. The randomisation sequence will be held centrally at Imperial College London by the CI's ([name] and [name]) who are not involved in the study visits and data analysis.

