## 2. STUDY OBJECTIVES

### Primary Outcome:

Change in serum LH following intranasal administration of kisspeptin compared to placebo. Blood samples will be taken at baseline (pre-administration) and every 15 minutes for 4 hours.

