## 3. STUDY DESIGN

This is a randomised, double-blind, placebo-controlled, crossover study investigating the effects of intranasal kisspeptin administration on reproductive hormone release in healthy volunteers (men and women) and patients with reproductive disorders. The cross-over design has been chosen as it is the most rigorous method to determine a treatment effect, by minimising the effect of confounding variables. Each participant will be required to attend all study visits, hence serving as their own control.

**The study will recruit three groups of participants.** *Group A* will consist of healthy men with normal reproductive function and will also determine the optimal dose for intranasal kisspeptin administration. *Group B* will consist of healthy (ovulatory) women with normal reproductive function. *Group C* will consist of female patients with reduced reproductive function, such as HA. The groups will not be recruited in parallel, as the results from *Group A* will determine the optimal dosing for *Groups B* and *Groups C*.

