## **7. STATISTICS AND DATA ANALYSIS**

This will be the first study investigating the effects of intranasal kisspeptin administration on reproductive hormone release in humans. Our previous work in healthy volunteers demonstrates that intravenous kisspeptin increases serum LH (mean 10.2 IU/L and standard deviation 0.4 IU/L), compared with placebo administration (mean 2.0 IU/L, standard deviation 0.1 IU/L) (11), and we predict a similar response following intranasal administration. Therefore, using these data, with  $\alpha = 0.05$ , power = 0.8 and effect size = 0.997, we performed a power calculation resulting in a sample size of 10 participants per group (*Group A* and *Group B*). To allow for dropouts and exclusions (estimated to be around 20%), 12 participants per group (*Group A* and *Group B*) will be recruited. It should be noted that regarding patients with reproductive disorders (*Group C*), the sample size will depend upon the specific disorder. For instance, our previous work demonstrates that the gonadotropin response following kisspeptin administration is similar in patients with polycystic ovary syndrome versus healthy women but augmented in patients with hypothalamic amenorrhoea [unpublished data].

Hormone level data will be assessed for normality and appropriate statistical methods chosen. Continuous data will be reported as measures of central tendency and of spread (e.g., mean and standard error of the mean or median and interquartile range as appropriate). For all study groups, time profiles of hormone levels during the 4-hour study period will be compared using two-way ANOVA with Bonferroni multiple comparison test [if the data is parametric], or Kruskal-Wallis test [if the data is non-parametric]. Mean responses (e.g., maximal increase and area under curve) will be compared using one-way ANOVA with Bonferroni multiple comparison test (*Group A*) and paired t-tests (*Group B* and *Group C*) [if the data is parametric] or Kruskal-Wallis test (*Group A*) and Wilcoxon signed-rank test (*Group B* and *Group C*) [if the data is non-parametric].  $P < 0.05$  will be considered statistically significant.

Data and all appropriate documentation will be stored for a minimum of 10 years after the completion of the study, including the follow-up period.

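### Group A has five visits with three pre-dose LH samples each, yet its summary analysis uses the visit baseline at most by subtraction. A covariate would cost little and could gain power.

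*Protocol*

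**What the plan says.** Section 3 (Study Visits, paragraph for all groups) sets three pre-dose samples per visit: "Blood will then be sampled at timepoints -30, -15, and 0 minutes (pre-administration baseline". In Group A each man attends five visits, four active doses and placebo, in random order. The design rests on within-person comparison: "Each participant will be required to attend all study visits, hence serving as their own control".

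The primary outcome in section 2 is worded as a change: "Change in serum LH following intranasal administration of kisspeptin compared to placebo". Section 7 gives the Group A test for the summary measures: "Mean responses (e.g., maximal increase and area under curve) will be compared using one-way ANOVA with Bonferroni multiple comparison test". Groups B and C get paired t-tests. For all groups, "time profiles of hormone levels during the 4-hour study period will be compared using two-way ANOVA with Bonferroni multiple comparison test". Rank-based tests replace these if the data are not normal.

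None of the named tests carries a baseline covariate. The protocol does not say how the three pre-dose values form one baseline, or whether AUC is corrected for it.

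**The concern.** Comparing a man with himself removes his stable LH level. It does not remove visit-to-visit movement in that level, which the three pre-dose samples measure directly.

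Subtracting the baseline assumes that a unit difference in baseline carries through as a unit difference in response. If the true slope is lower, subtraction adds noise. If AUC is left uncorrected, whatever the baseline could explain stays in the error term. A covariate estimates the slope instead of fixing it at 1 or 0.

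The price is one degree of freedom plus the error in the estimated slope, and it depends on how many within-person residual degrees of freedom there are. Group A, with five visits per man, has many more than Groups B and C with two. Group A also supplies the dose used in Groups B and C, chosen on maximal LH rise, so noise in its comparisons carries forward.

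**Working it through.** **Inputs from section 7.** Alpha 0.05; "power = 0.8 and effect size = 0.997"; 10 evaluable and 12 recruited in each of Groups A and B.

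**Assumptions, because the protocol gives no figure:**
- r, the within-person correlation between visit baseline and post-dose response (for two visits, between their paired differences).
- k, the ratio of baseline spread to response spread, within person.
- Two-sided tests.
- Four Bonferroni comparisons in Group A (each dose against placebo), so alpha per comparison = 0.05/4 = 0.0125.

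**Step 1. The plan's own figure.** A paired t-test with standardised difference 0.997 and two-sided 0.05 has power 74.6% at n = 9 and 80.1% at n = 10. The stated 10 reproduces, with no covariate gain assumed.

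**Step 2. Residual degrees of freedom in Group A.** Ten men × 5 visits = 50 values. Removing the mean (1), participants (9) and treatments (4) leaves 36, or 35 with the covariate. Fitting visit order takes 4 more, leaving 32 (31 with the covariate).

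**Step 3. Variance factors,** relative to the unadjusted within-person response:
- unadjusted: 1
- change score: 1 + k² − 2rk
- covariate: (1 − r²)(1 + 1/34), where 1/34 is the cost of estimating the slope

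**Step 4. Power in Group A, n = 10.** The noncentrality is 0.997 × √10 / √factor. Unadjusted it is 3.153, against a critical t of 2.629 on 36 df. For the covariate at r = 0.5 the factor is 0.75 × 1.0294 = 0.772 and the noncentrality 3.588, against 2.633 on 35 df.

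| r | Unadjusted | Change, k = 1 | Change, k = 0.5 | Change, k = 0.25 | Covariate |
|---|---|---|---|---|---|
| 0 | 0.70 | 0.36 | 0.58 | 0.67 | 0.68 |
| 0.3 | 0.70 | 0.52 | 0.72 | 0.75 | 0.73 |
| 0.5 | 0.70 | 0.70 | 0.84 | 0.80 | 0.82 |
| 0.7 | 0.70 | 0.92 | 0.94 | 0.86 | 0.95 |

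Simulation of the five-visit design agrees to within about a point. Adding visit order to all three analyses lowers each power by about a point or less and leaves the comparison unchanged.

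**Step 5. Bounds in Group A.** Against the unadjusted analysis, the covariate loses at most about 2 points (0.70 to 0.68 at r = 0) and starts to gain at r of about 0.17. Against change scores, the change-score factor is smallest at k = r, where it equals 1 − r². The covariate's disadvantage therefore never exceeds its own cost, the factor 1 + 1/34 and one df. At r = k = 0.5 that is 0.84 against 0.82.

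**Step 6. The same check in Group B** (two visits, n = 10, no Bonferroni). The cost factor is 1 + 1/(n − 3) = 1 + 1/7 = 1.143, with 8 df instead of 9. From 80.1% unadjusted, covariate power is 73.4% at r = 0, 77.3% at r = 0.3, 84.6% at r = 0.5 and 94.9% at r = 0.7. Break-even is r of about 0.39 at n = 10 and 0.34 at n = 12. Against a change score set at 80.1%, k = 0.25 and r = 0.3 give the covariate 73.5%. Group C, with 6 patients, has fewer degrees of freedom still.

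**The case against.** The strongest case against is that the baseline is already used: the primary outcome is a change, one named summary is a rise, and each participant is his or her own control. A reader might infer that the plan ignores the pre-dose samples. It does not. What is left open is whether AUC is corrected, and whether subtraction is the best use of the baseline.

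A reader might also infer that adjustment is free precision in Groups A and B alike. Step 6 contradicts that for Group B. The spread quoted in section 7 points the same way: 0.4 IU/L after kisspeptin and 0.1 on placebo. If baselines vary like placebo values and visits are independent, k is about √(0.1² + 0.1²)/√(0.4² + 0.1²) = 0.34, where a change score does well. In simulation at n = 10 and r = 0.3 the change score had 0.837 and the covariate 0.780, a loss of about 6 points. This objection stands for Groups B and C.

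Finally, covariates are often left to a statistical analysis plan, and one may exist here. That limits the weight of the point. But section 7 names specific tests, and the only latitude it gives is tied to distribution: "Hormone level data will be assessed for normality and appropriate statistical methods chosen".

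**Conclusion.** The point holds for Group A only, as a matter of efficiency. With 10 men and an effect of 0.997 SD, the covariate costs at most about 2 points of power. Against an unadjusted response it gains about 3 points at r = 0.3, 12 at r = 0.5 and 25 at r = 0.7. Against change scores it runs from about 2 points worse to much better, depending on r and k. Both are assumptions; the protocol gives neither.

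These figures credit the unadjusted analysis with participant effects. Read literally, a one-way ANOVA has none; that is a separate and more basic matter, and the gains above do not include it. The value 0.997 serves only as the plan's own planning figure, and its derivation is not examined here.

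A reader might take this as a finding of bias or of an invalid test. Nothing in the protocol supports that: visit order is randomised, so both the unadjusted and the change-score contrasts estimate the treatment effect. In Groups B and C the gain is uncertain in sign, and no change is called for.

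**What to change.** For Group A, replace the one-way ANOVA on the summary measures with a within-participant model for peak LH and AUC. Fit participant, visit order and treatment, with the visit's mean pre-dose LH (−30, −15 and 0 minutes) as a covariate, and keep Bonferroni for the dose-against-placebo contrasts. With that baseline in the model, peak LH and rise from the same baseline give the same treatment contrast, so the change outcome need not be redefined.

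For all groups, state that the baseline is the mean of the three pre-dose values, and whether AUC is baseline-corrected. In Groups B and C keep the simple paired contrast as primary.

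The cost is analysis wording and one residual degree of freedom in Group A. The samples are already planned. The wording should be fixed before unblinding.

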### **Safety of participants during the Study**

Participants will remain in the investigation unit for a short period of observation after termination of the study visit. At least two clinically trained investigators will be present throughout each study visit. During the study, blood pressure, and heart rate measurements will be taken at 15-minute intervals. Participants will be encouraged to report any unusual or unpleasant sensation to the investigators immediately. Any significant adverse effects will lead to withdrawal of the individual and any serious adverse effects will terminate the whole study.

Throughout the study there will be at least one physician available 24 hours per day via a direct line, with a second physician on back up, and a secondary direct line to one of the senior physicians. Although we do not anticipate any serious adverse effects, participants will be provided with contact numbers and clear instructions that, if they feel unwell, they should call us. Kisspeptin is rapidly cleared (11, 12) and participants would not be anticipated to experience any delayed effects on completion of the study visit.

The Chief Investigators, [name] and [name], are on site, and any potential side-effects of the study will be reviewed regularly by [name] and [name] and the other main investigator for the study ([name]). The safety of the participants is of the highest importance throughout the study. An internal audit will be completed at the end of the study. Study efficacy and safety will be regularly reviewed in fortnightly meetings. A formal data monitoring committee is not necessary as kisspeptin has been given to over 500 human subjects and is safe and well tolerated. The study may be subject to audit by Imperial College London under their remit as sponsor and other regulatory bodies to ensure adherence to GCP and the UK Policy Framework for Health and Social Care Research.

### **Kisspeptin**

Kisspeptin is a naturally occurring and safe hormone, which is known to play a critical physiological role in human fertility (13, 14). Kisspeptin has been given safely to over 500 male and female participants in subcutaneous and intravenous form without side effects (15–18). Levels of kisspeptin in the circulation increase ~7,000-fold during normal pregnancy without any known adverse effects (19). We do not anticipate any adverse effects of the doses of kisspeptin proposed in the study, however if any serious adverse effects are noted at any time, we will immediately suspend the study, report to the sponsor and review continuation of the research with the research ethics committee. The intravenous half-life of kisspeptin is short (28 minutes) and if any unexpected adverse effects are encountered (not expected), we would expect these to resolve rapidly with supportive management.

Kisspeptin-54 is stored at -20°C as per manufacturer's guidelines. Freeze-dried kisspeptin-54 vials will be reconstituted on the morning of each study visit to produce a solution containing the target dose, which will be self-administered by the participant (under supervision of the clinical team) using a nasal spray device

The maximum doses of kisspeptin-54 administered will be 25.6nmol/kg. We have already administered these identical doses during our previous studies (8, 15, 16, 20) that have demonstrated to safely produce a biological effect without untoward side effects. Intranasal placebo administration will consist of saline (identical in volume and appearance to kisspeptin), thus respecting the study's double blinded design.

## **4. PARTICIPANT ENTRY**

### **4.1. PRE-REGISTRATION EVALUATIONS**

We will recruit individuals with intact and reduced/absent fertility who are aged ≥18 years old. We will advertise via print (including posters around university campuses, local and regional newspapers and magazines) and online advertisements, including social media, as well as collaborate with the Endocrinology and Reproductive Medicine Departments at Imperial College Healthcare NHS Trust to identify potential participants from clinics. Upon first contact,

potential participants will be provided with a Participant Information Sheet and a self-report questionnaire (returned to a secure and dedicated email address: [[contact]](mailto:[contact])), to identify any objective exclusion criteria. If this does not identify any objective exclusion criteria the individual will be invited to a 1-hour face-to-face screening visit, which will be carried out by an experienced Research Doctor or Research Nurse. The face-to-face screening visit will involve going through the details of the study, obtaining consent, taking relevant medical history, clinical examination, vital signs assessment, an ECG, and clinical laboratory testing.

During the screening visit, the study will be explained again in full, and the participant will be given the opportunity to ask any further questions they may have. Informed written consent will be taken before proceeding to any further assessment. Participants will be informed that they are free to withdraw from the study at any time.

Blood samples will be collected for investigations including reproductive hormone levels, haematology, and biochemistry, if the participant consents.

Any new diagnoses that are made will be discussed with the participant by one of the study doctors and if the participant consents, their GP will be contacted to arrange further management or specialist referral as appropriate.

## 4.2. INCLUSION AND EXCLUSION CRITERIA

### INCLUSION CRITERIA

#### Healthy volunteers (*Group A and Group B*)

1. Aged 18–70 years
2. Non-smokers
3. Free of current or past physical or psychiatric illness
4. Naive to psychoactive substances, prescribed or illicit, for a minimum of 6 months prior to screening.
5. Regular menstrual cycles (women)

#### For female patients with common reproductive disorders (*Group C*)

1. As above *PLUS*:
2. Patients diagnosed in accordance with established guidelines (e.g. Endocrine Society guidelines for hypothalamic amenorrhoea)

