## STUDY SUMMARY

|                         |                                                                                                                                                                                                                                                                                                                       |
|-------------------------|-----------------------------------------------------------------------------------------------------------------------------------------------------------------------------------------------------------------------------------------------------------------------------------------------------------------------|
| TITLE            | Investigating the Effects of Intranasal Kisspeptin Administration on Reproductive Hormone Secretion.                                                                                                                                                                                                                  |
| DESIGN           | Randomised, double-blind, placebo-controlled, crossover study comparing intranasal kisspeptin administration versus intranasal placebo on reproductive hormone release in humans.                                                                                                                                     |
| AIMS             | To investigate the effects of intranasal kisspeptin administration on reproductive hormone release in healthy volunteers (men and women) and female patients with reproductive disorders (including hypothalamic amenorrhoea).                                                                                 |
| OUTCOME MEASURES | Blood levels of reproductive hormones measured using automated chemiluminescent immunoassays at baseline and every 15 minutes for 4 hours. Safety monitoring: heart rate, blood pressure, and the presence of adverse symptoms measured using automated blood pressure monitor every 15 minutes for 4 hours           |
| POPULATION       | A minimum of 12 healthy volunteers (i.e., healthy men and healthy women) and 6 patients with reproductive disorders.                                                                                                                                                                                                  |

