| ELIGIBILITY      | Healthy volunteers (with normal reproductive function [men and women], including regular menstrual cycles and not taking hormonal contraception [women]). Patients with reproductive disorders, diagnosed in accordance with established guidelines (e.g. Endocrine Society guidelines for hypothalamic amenorrhoea). |
| DURATION         | Recruitment will stop when sufficient participant numbers have been enrolled to ensure the planned sample size has been achieved. The study will stop once all participants have completed the study protocol.                                                                                                        |

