### Pre-Study Visits

Recruited participants will be asked to abstain from alcohol, caffeine, and sexual activities from 22:00 before their study visits and to consume a normal breakfast on their study days. All study visits will start in the morning to control for circadian hormonal changes. Study visits for participants in *Group A* and participants in *Group C* (e.g., anovulatory women) will take place at least 1 week apart (to ensure washout). Study visits for participants in *Group B* will take place during the follicular phase of the menstrual cycle, i.e., days 2-10 inclusive (to control for reproductive hormone changes over the menstrual cycle).

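### Group C inherits the healthy-volunteer inclusion list without exception, including regular menstrual cycles, which no patient with hypothalamic amenorrhoea can meet

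*Protocol*

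**What the plan says.** Section 4.2 gives five inclusion criteria under the healthy-volunteer heading (Groups A and B): an age range, non-smoking, absence of illness, a period free of psychoactive substances, and cycle regularity for women. Two matter here. Item 3 reads "Free of current or past physical or psychiatric illness" and item 5 reads "Regular menstrual cycles (women".

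The Group C list that follows has two items. The first says that the criteria above apply, with an addition. The second is that addition: "Patients diagnosed in accordance with established guidelines (e.g. Endocrine Society guidelines for hypothalamic amenorrhoea". No carried-over item is waived or modified.

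Other parts of the protocol describe whom Group C is meant to contain:

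- Section 3 says the group "will consist of female patients with reduced reproductive function, such as HA".
- Pre-Study Visits, on visit spacing, describes Group C with the words "e.g., anovulatory women) will take place at least 1 week apart".
- The eligibility row of the Study Summary places the cycle condition in the sentence on healthy participants, "Healthy volunteers (with normal reproductive function [men and women], including regular menstrual cycles and not taking hormonal contraception [women", and deals with patients in a separate sentence that asks only for a guideline diagnosis.
- The population row gives the size: "A minimum of 12 healthy volunteers (i.e., healthy men and healthy women) and 6 patients with reproductive disorders".

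**The concern.** The inclusion criteria are the text a research doctor or nurse applies at the screening visit (section 4.1) and the text an auditor would check. If that text bars the patients the group was created to study, there are two outcomes. Either such patients are enrolled as eligibility deviations, or each investigator decides which inherited items to ignore.

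The second outcome is more than a formality. Common sense can cancel the regular-cycle item, but it does not settle how far the illness item reaches. The protocol does not say whether an amenorrhoeic woman with a past psychiatric illness, or with a second physical condition, may enter. Eligibility also has a stated consequence: under section 6, a change in eligibility leads to exclusion from further participation. Group C is the trial's only patient group, so who may enter it should not depend on individual interpretation.

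**Working it through.** The protocol gives no figure to reproduce. The check is whether a patient can satisfy all the Group C criteria at once.

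**Step 1: what is inherited.** The carry-over line has no exception, so Group C eligibility is the five healthy-volunteer items together with a guideline diagnosis. The restriction of item 5 to women gives no way out, because sections 3 and 4.2 both define Group C as female.

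**Step 2: test each item against a woman with hypothalamic amenorrhoea.**

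| Inherited item | Compatible with the diagnosis? |
|---|---|
| 1. Age 18–70 | Yes |
| 2. Non-smoker | Yes |
| 3. No current or past illness | No, if the disorder counts as a physical illness; otherwise yes |
| 4. No psychoactive substances for 6 months | Yes |
| 5. Regular menstrual cycles | No: amenorrhoea means absence of menstruation |

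Item 5 alone leaves no eligible patient with this diagnosis. Item 3 adds a second conflict only under one reading of illness.

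**Step 3: compare with the rest of the protocol.**

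| Place | What it implies for Group C |
|---|---|
| Section 4.2 | Regular cycles required |
| Study Summary, eligibility row | Regular cycles required of healthy women only |
| Section 3 | Reduced reproductive function, with hypothalamic amenorrhoea as the example |
| Pre-Study Visits | Anovulatory women as the example; visits spaced by at least a week, as for the men, and not tied to cycle days 2–10 as for Group B |

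The visit schedule is telling. Group B visits are timed to the menstrual cycle and Group C visits are not, which fits a group without regular cycles. Section 4.2 is the outlier.

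**Step 4: how many patients are affected.** The plan is for at least six patients with reproductive disorders. Hypothalamic amenorrhoea is given as an example, and section 7 says the Group C sample size will depend on the specific disorder. No share with amenorrhoea, or with any other disorder without regular cycles, is stated. The affected number therefore cannot be calculated from the protocol.

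**The case against.** The best reply is that the intent is plain. The regular-cycle item sits under a heading for healthy volunteers, the Study Summary separates the two populations correctly, and the Group C list itself names hypothalamic amenorrhoea. An investigator who reads the whole protocol would not turn away an amenorrhoeic woman for lacking regular cycles. It can also be said that a patient list asking for a diagnosis implicitly exempts that diagnosis from the illness item.

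Much of this stands. It is probably a drafting slip, and it is unlikely that Group C would fail to recruit because of it. The point about the illness item is fair too, which is why that item is only secondary here. What does not stand is that clear intent repairs the text: nothing in the protocol waives item 5, and inclusion criteria are meant to be followed as written.

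A reader might infer more than the protocol supports:

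- *That affected patients would be dropped from the analysis.* The protocol defines no analysis set that removes ineligible participants. Section 6 concerns further participation, not analysis.
- *That only women with a mild disorder and regular cycles could comply, so that the population shifts.* No such subgroup is described, and if item 3 is read as covering the disorder, it would bar these women too.
- *That all six planned patients are ineligible.* The six are patients with reproductive disorders, and the protocol does not say that all have amenorrhoea.

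**Conclusion.** The point holds as an internal contradiction in operative eligibility text. Followed exactly, section 4.2 excludes every patient with the one disorder it names, and it conflicts with the Study Summary, section 3 and Pre-Study Visits.

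The conclusion rests on two things: that the carry-over line means what it says, and that amenorrhoea cannot coexist with regular cycles. It does not depend on the illness item, which conflicts only if the reproductive disorder is classed as an illness.

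The consequence is that each enrolled patient with hypothalamic amenorrhoea, or with another disorder without regular cycles, would be an eligibility deviation. The share of Group C is not stated. Nothing here bears on Groups A and B, the primary outcome, power or type I error. It should be corrected before Group C recruitment because it concerns who may enter the only patient group.

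**What to change.** Reconcile section 4.2 with the Study Summary, section 3 and Pre-Study Visits. Replace the carry-over line in the Group C list with that group's own inclusion items:

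- keep the age, smoking and psychoactive-substance items;
- keep the illness item, adding that it does not refer to the reproductive disorder under study;
- omit the regular-cycle item, as the Study Summary already does for patients;
- keep the guideline diagnosis.

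The cost is a short protocol correction. No sample size, visit, measurement or analysis changes.
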